##### Delivery of evidence-based treatments

The percentage of evidence-based content and quality of delivery of therapy in a 10 % random subset of sessions assessed by coding audio-taped therapy sessions will be compared between groups using an analysis of variance (ANOVA) model, following the method used in the trial in the USA study [30].

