New Zealand’s Child and Adolescent Mental Health Services (CAMHS) provide secondary level services for the 3–5 % of those with the most severe mental health problems aged 0–19 years [17]. The two largest professional groups employed in these services are nurses and social workers [18]; however, their pre-registration courses do not include training in psychotherapies specifically for youth [19]. Therefore, most learning occurs ‘on the job’. Furthermore, for clinicians to effectively treat a diverse caseload, they would need to train in multiple therapies, which is expensive and takes several years. For example, training in cognitive behavioral therapy is available in New Zealand in a one-year postgraduate course, which can be accessed by up to 12 clinicians per year. Accredited training in ‘Incredible Years’ (a form of evidence-based parent management training [20]) takes a year to complete and can be accessed by about 35 clinicians per year. Little training is available outside these courses and what exists will reach only a small minority of the approximately 1,000 full-time equivalent CAMHS clinicians in New Zealand [18]. The extent to which evidence-based therapies are currently used in CAMHS is not known, but based on clinicians’ access to training, and from overseas research [21–23], it is likely to vary across services and be limited by staff members’ past training, and may not be acceptable or effective for Māori (the indigenous people of New Zealand) or Pacific (people from the Pacific region) populations. Moreover, to meet the projected doubling of the demand on mental health services by 2020, treatment needs to be delivered more effectively and efficiently [24].

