## Methods

### Design

This study is a multi-site effectiveness randomized controlled trial comparing MATCH-ADTC with usual care [41]. Prior to randomization, written informed consent is obtained from each participant. Randomization is implemented on two levels: first, randomization of participating clinicians, then randomization of youth participants. For the randomization of clinicians, all clinicians from participating services were invited to participate and provide written informed consent. Consenting clinicians were block randomized (by service or team) in a 1:1 ratio to MATCH-ADTC or usual care. The block size varied across sites, depending on the number of individual clinicians recruited from each site. Clinicians were stratified on the basis of previous training in evidence-based therapies (i.e., those with versus those without training in cognitive behavioral therapy or behavioral parent training). Clinicians randomized to MATCH-ADTC received training in MATCH-ADTC at the beginning of the study prior to the recruitment of youth participants. Those randomized to usual care will receive training at the end of the study (once all follow-up data have been collected). Randomization of youth participants occurs after a clinician-administered eligibility check and once written consent has been obtained. Youth participants are then randomized in a 1:1 ratio to receive MATCH-ADTC or usual care, with participants stratified by sex and ethnicity (Māori, Pacific, or ‘other’). Web-based randomization procedures are used to determine treatment allocation. Data from all participants will be included in data analysis, irrespective of whether or not all assessments have been completed.

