#### Primary outcomes

##### Clinical outcomes

The difference in the trajectories between groups will be tested using a mixed effects regression model: *a*_0_ (intercept) + *a*_1_ (participant) + *a*_2_ (treatment group) + *a*_3_ (time) + *a*_4_ (treatment × time) and intercept and participant as random effects. These analyses will further include terms for:Service type (i.e., Kaupapa Māori, Pacific and ‘mainstream’ CAMHS);Clinicians’ previous training in evidence-based therapy;Baseline symptom level; andMedication use.

Although we are now unable to conduct ethnic-specific analysis, summary data will be used to illustrate whether there is a broad consistency of the clinical outcome results across ethnicity groups.

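### The ANOVA for evidence-based content names neither prior training nor service/team, the clinician randomisation factors; whether its standard errors come out too wide or too narrow depends on the unit of analysis

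*Protocol article*

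**What the plan says.** Protocol article, Design: "Consenting clinicians were block randomized (by service or team) in a 1:1 ratio to MATCH-ADTC or usual care". The same paragraph adds: "Clinicians were stratified on the basis of previous training in evidence-based therapies", defined as training in cognitive behavioral therapy or behavioral parent training.

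On how far evidence-based therapy is used in these services at present, the Background says that "it is likely to vary across services and be limited by staff members’ past training". It gives no size for either influence and says that the present extent of use is unknown.

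Under Clinical outcomes, the mixed model for the parent-rated Brief Problem Monitor lists further terms. They include "Clinicians’ previous training in evidence-based therapy" and a three-level service type, which is coarser than the service or team blocks.

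Under Delivery of evidence-based treatments, the percentage of evidence-based content and the quality of delivery in a 10 % random subset of sessions "will be compared between groups using an analysis of variance (ANOVA) model, following the method used in the trial in the USA study". No further term is listed, and neither the unit of analysis nor a clinician effect is stated.

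**The concern.** Evidence-based content is something clinicians do, and clinicians were randomised within strata that the article itself links to that behaviour. Such randomisation removes between-stratum differences from the true variance of the arm contrast. An analysis that ignores the strata leaves those differences in its error term. As written, the adjustment for prior training is attached to the symptom model but not to the model for therapist behaviour.

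At stake are the power and the error rate of the test of the second primary hypothesis. The scored unit is the session, and sessions are nested in youths and in clinicians. The strata therefore cannot be considered apart from clinician clustering, which can push the error the other way.

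**Working it through.** **The plan's own figures.** No power is stated for this outcome. The figures given for the clinical outcome reproduce but do not transfer:
- 200 participants, difference 2, SD 4.4: 2 / (4.4 × √(2/100)) = 3.21; Φ(3.21 − 1.96) = 0.895, against the stated 90 %.
- 60 clinicians, 400 patients, 15 % attrition, ICC 0.1: 400 × 0.85 = 340; 340/60 = 5.67 per clinician; design effect 1 + 4.67 × 0.1 = 1.467; detectable effect (1.96 + 0.84) × √(4 × 1.467/340) = 0.37, as stated.

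**Inputs.** From the article: 60 clinicians (C), ten clinics, 1:1 allocation. Assumed, because the article gives no variance figures for this outcome: total variance 1; share explained by training 5–20 % and by site 5–10 % (sum S); residual clinician ICC 0.1–0.3 (r); k = 3 or 5 coded sessions per clinician; true effect 0.5 SD. Session-level variance is v = 1 − S − r.

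**Variance of the arm contrast under balanced stratified allocation**
- True: (4/C)(r + v/k)
- Estimated from clinician means without strata: (4/C)(S + r + v/k), always too large when S > 0
- Estimated from sessions taken as independent, without strata: 4/(Ck). This is too small when (k − 1)r > S.
- Estimated from sessions with strata but no clinician term: (4/(Ck))(r + v). This is too small whenever r > 0 and k > 1.

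Example with S = 0.2, r = 0.1, k = 3, v = 0.7: true SE √(0.0667 × 0.333) = 0.149; clinician means without strata √(0.0667 × 0.533) = 0.189; sessions without strata √(4/180) = 0.149; sessions with strata √(0.0222 × 0.8) = 0.133.

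**Simulation** (permuted blocks within site and training, 1,500 runs per setting). Each cell shows the result without and then with the strata terms, in %.

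| k | Training / site share | r | Clinician means: type I error | Clinician means: power | Sessions as independent: type I error |
|---|---|---|---|---|---|
| 3 | 5 / 5 | 0.1 | 3.2 → 5.7 | 81.3 → 87.6 | 6.8 → 8.9 |
| 3 | 10 / 10 | 0.1 | 1.7 → 4.7 | 78.1 → 90.1 | 5.0 → 8.1 |
| 3 | 10 / 10 | 0.3 | 2.4 → 5.6 | 66.2 → 77.9 | 11.1 → 15.8 |
| 3 | 20 / 10 | 0.1 | 0.4 → 5.4 | 73.8 → 92.9 | 4.3 → 8.6 |
| 5 | 5 / 5 | 0.1 | 2.4 → 5.6 | 92.9 → 96.8 | 9.5 → 11.9 |
| 5 | 10 / 10 | 0.3 | 1.3 → 4.9 | 72.0 → 84.5 | 17.7 → 24.2 |

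Over all settings with r of 0.1 to 0.3, the clinician-level SE without strata is about 9–50 % too large. The power gain from adding the strata runs from 96.8 − 92.9 = 3.9 to 92.9 − 73.8 = 19.1 points.

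**Closer to the documented route.** A second simulation used 200 youths, 60 clinicians, ten sites and a 10 % sample of sessions, again with assumed variance shares. For clinician means, adding the strata moved type I error from about 2–4 % to 4–5 % and power from 56–76 % to 77–88 %. For sessions treated as independent, type I error was about 14–30 % without the strata and 12–29 % with them.

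**The case against.** The strongest reply is that the omission is read from silence. The section does not say that the ANOVA is one-way. It defers to the USA trial's method, and a journal article condenses a fuller plan. This stands in part: the term list may be fuller elsewhere. But the article does list adjustment terms for the outcome described immediately before, and the USA method cannot supply this trial's own service or team blocks.

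A second reply is that a conservative test with an unbiased estimate is an efficiency matter, and that comparability with the USA trial is a stated aim. Both parts are fair for a clinician-level analysis, and the second is met by keeping the USA-style ANOVA as a sensitivity analysis.

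A third is that a term for every service is heavy for this sample. With 15 % clinician attrition, 60 × 0.85 = 51 clinicians remain, about five per clinic, so pooling of very small teams has to be allowed.

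Two stronger readings are tempting:
- A reader might infer that the planned standard errors are simply too large. The article does not support that, because it scores sessions and nowhere says that clinician means are analysed. With sessions as the unit, the error is usually in the opposite direction.
- A reader might infer that prior training and service affect this outcome more than any other. The Background only calls the influence likely and describes existing services. The manual and weekly expert supervision in the MATCH-ADTC arm could weaken it there.

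**Conclusion.** The point holds in a conditional form. The section names neither clinician randomisation factor for an outcome that the article expects both to influence, and the consequence depends on the unit of analysis.

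- **Clinicians as the unit:** the test is conservative (type I error 0.4–3.2 % instead of 5 % in the main simulation) and loses roughly 4 to 20 points of power. Leaving the factors out does not bias the estimate.
- **Sessions as the unit, taken as independent:** clinician clustering dominates. Type I error was 4–18 % without the strata and 8–24 % with them in the main simulation, and higher in the one closer to the documented route. The exceptions are settings with few coded sessions, low ICC and large strata shares, where the analysis without strata is near or slightly below 5 %.

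All sizes rest on assumed variance shares, ICCs, session counts and a 0.5 SD effect. The directions follow from the variance formulas. The strata terms are worth adding, but they give a valid test only together with a provision for clinician clustering.

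**What to change.** In Delivery of evidence-based treatments, replace the ANOVA sentence with a model specification for both evidence-based content and quality of delivery. It should have terms for treatment group, clinician prior evidence-based training (yes/no) and service/team as used for blocking, with a rule set in advance for pooling very small teams. It should also include a clinician random effect, or else analyse clinician means. Keep the USA-style ANOVA as a sensitivity analysis for comparison with that trial.

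The cost is one sentence of wording and about ten degrees of freedom (one for training, nine for ten services). With 51 clinicians this leaves 51 − 12 = 39 residual degrees of freedom in an analysis of clinician means. No new data are needed, since both factors had to be known in order to randomise the clinicians.

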##### Efficiency of service delivery

Efficiency in delivery of therapy for MATCH-ADTC and usual care will be compared using ANOVA to test for significant differences using the following data which will be collected from the clinical service, including:Clinician time (in minutes);Duration of contact with the service (in weeks);Number of therapy sessions; andNumber of missed therapy sessions.

If any of these outcomes do not meet the assumptions for parametric ANOVA models, the data will be transformed as appropriate prior to analysis.

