### Outcomes and measures

#### Primary outcomes

The three primary outcomes each address one of the three central aims of the trial: (i) the difference in trajectory of change of clinical severity between groups, using the parent-rated Brief Problem Monitor [42]; (ii) clinicians’ use of evidence-based content during therapy sessions (based on audio-recorded therapy sessions); (iii) total time spent by clinicians delivering therapy (using therapy logs).

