One of the practical challenges for this study is determining the end of treatment because services have different guidelines in place regarding discharge (e.g., a case can be left open for a number of weeks after a proposed final session, in case a youth and their family would like an extra ‘top-up’ session). If needed, the regular weekly assessments and the therapy log data will allow us to determine retrospectively when treatment ended and link this to the correct weekly telephone administered assessments. Another issue has been the recruitment of youths at Māori and Pacific sites. The challenges that impacted on recruitment of these groups included the smaller pool of clinicians at Kaupapa Māori and Pacific services, the smaller proportion of youths meeting study criteria because of high acuity of the problems (including suicidality) and the lower numbers of youths within our age range.

This is a pragmatic trial [41] and accordingly the exclusion criteria have been kept to a minimum and youth participants’ presentation (not their diagnoses) have determined eligibility for participation in the study. As such, we believe this study will have good external validity, because the participants reflect the heterogeneity of youth from ‘real-life’ clinical services. Hence the findings will be applicable to other CAMHS in New Zealand and will probably be of relevance to other countries that have a comparable healthcare workforce and service delivery models.

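### The efficiency comparison, which carries primary outcome (iii), names no baseline covariates and so gives up some precision that recorded data could supply

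*Protocol article*

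**What the plan says.** The Primary outcomes section makes total therapy time by clinicians, taken from the therapy log, the third primary outcome. Under Efficiency of service delivery, this measure and three others (weeks of contact, number of sessions, missed sessions) share one analysis: "Efficiency in delivery of therapy for MATCH-ADTC and usual care will be compared using ANOVA to test for significant differences". The only provision added is "If any of these outcomes do not meet the assumptions for parametric ANOVA models, the data will be transformed as appropriate prior to analysis".

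The Clinical outcomes subsection, under the same Primary outcomes heading of the statistical methods, goes further. After the mixed model it says "These analyses will further include terms for" service type, clinicians' previous training, "Baseline symptom level" and medication use. That list is attached to the clinical model only.

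Three other places bear on the point. The Design section has youths randomized 1:1, "with participants stratified by sex and ethnicity". Table 1 schedules the Brief Problem Monitor at baseline. The Discussion says that "services have different guidelines in place regarding discharge", and that a case may stay open for some weeks after what was meant to be the last session.

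**The concern.** The amount of therapy a youth receives plausibly depends on severity at entry and on the service that treats them. When such variables are left out, the variation they explain stays in the residual and widens the interval for the arm difference. The article recognises this for the clinical outcome but names nothing comparable for efficiency.

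Precision matters here for two reasons. The recruitment target was halved from 400 to 200 with power worked out for the Brief Problem Monitor only, and the article gives no power figure for clinician time. Hypothesis (iii) is that efficiency is equal or better, and a wide interval says little about that.

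**Working it through.** **Inputs from the article.** 200 youths, 1:1, so 100 per arm; two-sided α of 0.05; SD of 4.4 and difference of 2 units for change in the parent-rated Brief Problem Monitor; 15 % attrition and an intraclass coefficient of 0.1 for youths within clinicians (both from the initial sample size calculation); at least 60 clinicians.

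**Assumed.** R², the share of variance in clinician time explained by the baseline covariates, is not given. The range used is 0.01 to 0.30.

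**Step 1: the article's own figures.** Power = Φ(δ / (SD·√(2/n)) − 1.96).
- 100 per arm: 2 / (4.4 × √0.02) = 3.214; Φ(1.254) = 89.5 %, against 90 % stated.
- 80 per arm: 2 / (4.4 × √0.025) = 2.875; Φ(0.915) = 82.0 %, against 80 % stated.

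Both agree to within about two points. They concern the clinical outcome, not efficiency.

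**Step 2: efficiency without covariates.** The standardized difference detectable with 80 % power is (1.960 + 0.842) × √(4/200) = 0.396 SD. With 15 % attrition (170 youths) it is 0.430 SD.

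**Step 3: efficiency with covariates.** The residual variance is multiplied by (1 − R²), the standard error by √(1 − R²), and the equivalent sample size is 200 / (1 − R²). Power is for the 0.396 SD difference.

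| Assumed R² | SE factor | Equivalent N | Detectable difference (SD) | Power |
|---|---|---|---|---|
| 0 | 1.000 | 200 | 0.396 | 80.0 % |
| 0.01 | 0.995 | 202 | 0.394 | 80.4 % |
| 0.05 | 0.975 | 211 | 0.386 | 82.0 % |
| 0.10 | 0.949 | 222 | 0.376 | 84.0 % |
| 0.20 | 0.894 | 250 | 0.354 | 87.9 % |
| 0.30 | 0.837 | 286 | 0.331 | 91.8 % |

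**Step 4: clustering, which step 3 ignores.** With 60 clinicians there are 200/60 = 3.3 youths each. If the coefficient of 0.1 also holds for minutes (an assumption), the design effect is 1 + (3.33 − 1) × 0.1 = 1.23, and the true standard error is √1.23 = 1.11 times the one computed under independence. Combined with step 3, relative to the independence standard error without covariates: 0.949 × 1.11 = 1.05 at R² = 0.10; 0.894 × 1.11 = 0.99 at 0.20; 0.837 × 1.11 = 0.93 at 0.30. A model that adds covariates but still treats youths as independent would report too narrow an interval.

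**The case against.** The strongest reply is that the article says only ANOVA. It does not say one-way or unadjusted; an ANOVA can carry factors, and a covariate list is often left to an analysis plan. Even a one-way ANOVA is a valid comparison of randomized youths. Its validity stands. The appeal to the analysis plan stands only in part: the article does list covariates for one primary outcome and fixes a method without any for another, so adding them is a concrete improvement to what is written, not a complaint about missing detail.

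Three stronger readings are tempting and not supported.

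- *A reader might infer that differing discharge rules distort the primary outcome.* The therapy log records the date and length in minutes of each session. A case held open after its last session adds weeks but no minutes, unless a further session takes place. The argument therefore bears mainly on weeks of contact. The Discussion also says that the weekly assessments and logs can be used, if needed, to fix the end of treatment retrospectively.
- *A reader might infer bias because youths are not stratified by clinic.* Chance imbalance between clinics is part of the random error that the standard error already covers. It is the same noise that adjustment would reduce, not a further problem.
- *A reader might infer that adjustment settles the hypothesis of equal or better efficiency.* Whether a test for differences suits that hypothesis is a separate question, which covariates do not answer.

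It also stands that no document shows the gain to be large enough to change a conclusion.

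**Conclusion.** The point holds as a modest, low-cost improvement. As written, the efficiency analysis, including primary outcome (iii), names no covariates although suitable ones are recorded, and so gives up precision. It is not biased or invalid on that account.

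The size is conditional. It rests wholly on an assumed R²: negligible at 0.01 to 0.05 (power from 80 % to at most 82.0 %), worthwhile from about 0.10 (84.0 %), and substantial at 0.30 (91.8 %). These figures assume independent youths. If the article's intraclass coefficient applies to minutes, allowing for clinicians offsets most or all of the gain up to R² of about 0.20, when set against an ANOVA that ignores clustering. The documents do not support a claim that a definite amount of power is being lost.

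**What to change.** Under Efficiency of service delivery, replace the ANOVA by a prespecified linear mixed model for each efficiency measure, on the scale chosen under the existing transformation rule, with:

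- fixed effects for arm, baseline parent-rated Brief Problem Monitor, sex, ethnicity and service (clinic with small clinics pooled, or service type);
- a random effect for clinician, in line with the clustering assumed in the Sample size section.

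Report the adjusted arm difference with its 95 % confidence interval. Use baseline variables only. The medication term in the clinical model should not be carried over unless it means use at baseline, since later use may be affected by treatment. The article describes baseline measurement after randomization, so the text should say that the baseline score is the one taken before therapy starts.

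**Cost.** A sentence or two, and no new data. With service type the covariates use 1 + 1 + 2 + 2 = 6 degrees of freedom; with all ten clinics unpooled they would use 1 + 1 + 2 + 9 = 13, of 200 youths. Service type and ethnicity may overlap, which would reduce the gain. The clinician term may widen the interval, but that width would then reflect the clustering the article itself assumes.

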## Discussion

This trial has been designed to balance the need to replicate the evaluation of MATCH-ADTC conducted in the USA with the objective of evaluating it in a New Zealand context. We anticipate that if results are positive, MATCH-ADTC may become part of core training for CAMHS clinicians, resulting in better outcomes for youth with mental health challenges, increase in delivery of evidence-based treatments, and improved efficiency of service delivery. This trial therefore has practical implications for the workforce, as MATCH-ADTC is the first comprehensive evidence-based system that could realistically become part of a ‘core competency’ training package for all CAMHS clinicians.

We selected brief measures to keep the weekly telephone assessments as brief as possible, and lessen participant burden. Frequent assessments allow for monitoring of change when treatment duration varies considerably and the end of treatment is unknown. We have used an online diagnostic tool because we do not have dedicated researchers at each site, and because formal diagnoses are not routinely obtained in each CAMHS in New Zealand. In return for the time taken to complete the assessment, and to maximize Development and Well-Being Assessment completion, we have chosen (with ethics committee approval) to incentivize families with gift vouchers. Each family received a NZ$30 (approximately US$20) supermarket gift voucher for completing the Development and Well-Being Assessment at baseline and a second NZ$30 voucher after intervention. Those who completed both the baseline and the post-intervention Development and Well-Being Assessment received an additional NZ$30 (in total NZ$90). These gift vouchers were provided as a gratuity for the time taken to complete these assessments.

Most CAMHS in New Zealand structure their services using the Choice and Partnership Approach [58], in which an intake clinician conducts the initial assessment to determine whether the treatment at CAMHS is suitable for the young person, and then a treatment clinician is allocated and therapy is provided by the allocated clinician. This allows for a screening assessment and for randomization at the intake session without disrupting the rapport established between the family and the clinician, as the allocated clinician usually differs from the intake clinician.

One of the practical challenges for this study is determining the end of treatment because services have different guidelines in place regarding discharge (e.g., a case can be left open for a number of weeks after a proposed final session, in case a youth and their family would like an extra ‘top-up’ session). If needed, the regular weekly assessments and the therapy log data will allow us to determine retrospectively when treatment ended and link this to the correct weekly telephone administered assessments. Another issue has been the recruitment of youths at Māori and Pacific sites. The challenges that impacted on recruitment of these groups included the smaller pool of clinicians at Kaupapa Māori and Pacific services, the smaller proportion of youths meeting study criteria because of high acuity of the problems (including suicidality) and the lower numbers of youths within our age range.

This is a pragmatic trial [41] and accordingly the exclusion criteria have been kept to a minimum and youth participants’ presentation (not their diagnoses) have determined eligibility for participation in the study. As such, we believe this study will have good external validity, because the participants reflect the heterogeneity of youth from ‘real-life’ clinical services. Hence the findings will be applicable to other CAMHS in New Zealand and will probably be of relevance to other countries that have a comparable healthcare workforce and service delivery models.

